## **eHBB + mHBS/DHIS2: Virtual reality technology and DHIS2 mobile data collection to improve newborn healthcare delivery in low and middle income countries**

### **1. STUDY OVERVIEW**

Neonatal mortality, or death among newborns 0-28 days, now accounts for approximately 44% of global under 5-years child mortality. Each year, there are 2.65 million stillbirths, and nearly 2.8 million newborn deaths, most of which are preventable. The majority of these deaths occur in low- and middle-income countries (LMICs). Intrapartum asphyxia is one of the three leading causes of neonatal mortality, and also underlies high rates of newborn morbidity. Training in neonatal resuscitation (NR) reduces asphyxia-related newborn mortality and morbidity, but there are barriers to the effective implementation of NR programs in LMICs, which are exacerbated by gaps in data collection of key indicators and outcomes.

However, the high penetration of mobile smartphones and cellular network connectivity in urban areas, along with new mobile graphics processing capabilities, makes innovative simulation training, including mobile-phone based virtual reality (VR), potentially feasible even in LMICs. Mobile VR simulations can be engaged at the learner's convenience, on their own smartphone, with game-based automated feedback that is ideal for episodic learning. Mobile VR training provides an opportunity to address challenges related to (a) maintenance of neonatal resuscitation knowledge and skills over time; (b) inconsistent migration of neonatal resuscitation skills into actual clinical practice; and (c) lack of a standardized dissemination to support neonatal resuscitation in LMICs.

We propose to use mobile VR simulations and a DHIS2-integrated mobile data collection platform as a tool to leapfrog over the current challenges to obtaining and maintaining NR knowledge and skills among health care providers (HCPs) in LMICs including lack of infrastructure, staff shortages, and high rates of staff turnover. Our hypotheses are that mobile phone-based VR training and digital data collection will provide: 1) effective training in neonatal resuscitation 2) an easy method to maintain skills, and 3) a less costly option of neonatal resuscitation training than current methods.

**Methodology:** To test these hypotheses we will conduct a randomized controlled trial of the VR neonatal resuscitation module in healthcare providers in Nigeria and Kenya to assess the impact of module on neonatal resuscitation performance.

**Outcome variables:** We will assess healthcare provider knowledge and performance of neonatal resuscitation in educational (simulation) and clinical settings and compare this performance across study groups.

## 2. BACKGROUND

*Helping Babies Breathe* (HBB) is a neonatal resuscitation training program for health care providers (HCPs) in LMICs. Since its global launch in June 2010, HBB has rolled out in over 80 countries worldwide. Helping Babies Breathe (HBB) training is conducted using a dissemination model called “training of trainers” (TOTs), which involves one to three days of in-person training of future trainers or providers of neonatal resuscitation through the use of lectures, small group learning, hands-on practice among paired learners using low-tech manikins, and evaluation of participants’ knowledge and skills using a multiple choice questionnaire, skills checks, and objective structured clinical examinations. However, field studies demonstrate that initial HBB training alone is insufficient for transfer of skills to clinical practice. In the absence of continued mentoring and a supportive environment after the course, there is often a failure, among HBB providers, to consolidate and maintain the required knowledge, skills, and performance competencies which are required in order to perform high-quality neonatal resuscitation (NR) during actual clinical practice.

Access to mobile phones, including smart phones and devices, has become nearly ubiquitous in LMICs allowing the introduction of e-learning that increases availability, scalability, flexibility and efficiency while decreasing marginal costs for training. Evidence shows that e-learning is generally as effective as traditional teaching methods. Under the right conditions, e-learning has the ability to promote innovations in design and distribution, including interactive learning, problem based learning, and standardized feedback. Computer-based simulations, a subset of e-learning strategies, are increasingly used for self-directed learning before, or after attending an in-person course, e.g. [HeartCode® ACLS](#), [HeartCode® PALS](#) and [NRP eSim®](#) programs.

Mobile VR simulations can be delivered on mobile phones as *screen-based* experiences transformed into *immersive* experiences with the use of a low-cost VR headset. Typically, they are brief, engaging, interactive, experiences that are relevant to clinical practice with the goal of fostering experiential learning that transforms attitudes and behaviors. VR simulations use a strategy of deliberate practice similar to the Ericsson’s deliberate practice paradigm, in which learners deliberately practice their skills with expert coaching and feedback until they are able to perform the skills with minimal coaching. In games, automated feedback is tailored to the learner’s performance to ensure that practice occurs until the learner achieves the skills needed to move on to the next level of difficulty.

Integrating mobile VR training and digital data collection with neonatal resuscitation training in LMICs will address the challenges of (a) maintenance of knowledge and skills over time; (b) inconsistent migration of competencies into actual clinical practice; and (c) lack of a standardized, integrated, bi-directional data collection and information dissemination platform to support training in LMICS. The use of mobile VR simulations in HBB programs potentially

represents increased access to training, opportunities for self-directed learning, and less costly skill maintenance.

Investigators at the University of Washington have co-developed a virtual Helping Babies Breathe (eHBB) training simulation with Oxford University on the Life-Saving Instruction for Emergencies (LIFE) platform. A game-like approach utilizing a 3D game engine allows the user to experience an immersive and engaging training experience that has been adapted for the proposed eHBB (electronic Helping Babies Breathe) module. eHBB will run on a mobile phone but will also include the capability to work with low-cost VR headsets. In addition, investigators at Indiana University are customizing the mHBS (mobile Helping Babies Survive) application, an expanded version of an existing open-source data collection application mHBB to deliver the eHBB training module. The integrated eHBB and mHBS module will be used to augment initial and refresher training on key NR knowledge, skills and competencies among HCPs in LMICs.

### 3. STUDY OBJECTIVE

The primary objective is to assess the impact of mobile VR simulation used before and after initial NR training on neonatal resuscitation educational indicators and performance outcomes in healthcare providers, in comparison to traditional HBB training.

## 4. STUDY PROCEDURES

### 4.1 STUDY PARTICIPANTS

Our overall target sample size is 250 participants, but we will recruit up to 280 total participants across two international sites with an estimated 140 participants per site to account for attrition. Potential study participants will be identified from individuals registered to take an in-person HBB course or because they work or are assigned rotations in the labor/delivery wards of participating facilities.

### 4.2 STUDY FACILITIES

Participants will be recruited at study sites in Nigeria and Kenya. Potential study sites currently identified include Lagos University Teaching Hospital and referring facilities: Randle General Hospital, Surulere, and Federal Medical Centre, Ebute-Meta, Lagos Island Maternity Hospital, Lagos Island, Harvey Rd. Health Center, Shomolu General Hospital, Mushin General Hospital, Isolo General Hospital, Regina Mundi Hospital, Mushin, R-Jolad Specialist Hospital, Lagos, Nigeria. These facilities were selected on the basis of delivery volumes; number of nursing staff; presence of a neonatal unit; and/or association with a nursing and/or midwifery training program.

### 4.3 INCLUSION CRITERIA

All HCPs who provide neonatal resuscitation to inborn or outborn infants and provide study consent. Key stakeholders in healthcare administration and community-based stakeholders will

also be recruited to participate in key informant interviews and focus group discussions.

#### 4.4 EXCLUSION CRITERIA

HCPs who have received NR training less than one year before enrollment in the study; individuals who do not provide neonatal resuscitation as part of their duties; or will be unavailable or unwilling to participate in follow-up study activities throughout the 6-month post-initial training period will be excluded.

#### 4.5 RECRUITMENT

Site coordinators or research assistants will identify potential study participants from HCPs working in study facilities that meet eligibility criteria and are enrolled in a study HBB course.

A convenience sample of key stakeholders within Nigeria and Kenya, such as health facility administrators and community-based stakeholders will also be recruited to participate in key informant interviews and focus group discussions. (Appendix 3, Recruitment information)

#### 4.6 INFORMED CONSENT

Site coordinators or research assistants will obtain informed consent from potential study participants. Each site is to provide their consent form to each study participant to be signed prior to randomization. (Appendix 4, Consent form).

#### 4.7 RANDOMIZATION/ALLOCATION PROCEDURE

Study numbers will be randomly generated, via a computer-generated algorithm for the VR, Educational (NR) video only, or Control (standard HBB TOT) groups. The eHBB study will be using block randomization based on provider experience: novice (no previous HBB training) and non-novice (any previous HBB training) to ensure that recruited participants are evenly distributed into all arms and groups of the study.

#### 4.8 OUTCOME MEASURES

The *HBB Knowledge check* is a standardized HBB tool, is an 18-item multiple choice questionnaire (MCQ) which assesses HCP knowledge regarding immediate care after birth, routine care, and basic neonatal resuscitation (Appendix 6, HBB Knowledge Check).

*BMV Checklist*: The bag-and-mask ventilation skills checklist (BMV) is a standardized HBB tool used to assess HCPs competency on the provision of positive pressure ventilation with a bag-and-mask device (Appendix 7, Simulation Checklists).

*Standardized simulations/OSCEs*: The HBB 2nd edition curriculum has two OSCEs, called OSCE A and OSCE B. These standardized simulations involve a series of time-sensitive tasks which happen in rapid succession and follow the steps of the HBB Action Plan (Appendix 7, Simulation Checklists).

*Delivery Checklist:* Routine newborn care provided by participating healthcare providers will be observed by research assistants using a standardized checklist.

## 5. STUDY INTERVENTIONS

### 5.1 PRE-COURSE INTERVENTIONS

Site coordinators or research assistants will provide links and airtime to download the mHBS/DHIS-2 application to their phone or a study device.

*Pre-survey:* The baseline HBB knowledge check and a demographic survey with questions regarding age, gender, area on duty, years of experience, previous health care, and NR training, time elapsed since NR previous training, experience/comfort with using computers, experience/comfort with video games, smartphone or tablet device ownership, will be administered through the mHBS application.

Completion of the pre-survey and baseline HBB knowledge check will “unlock” the study group assignment.

**Figure 2. Study Timeline**

[figure not shown]

*Study group assignment:* Participants will be given access to study materials based on their group assignment of VR (eHBB), NR video or Control groups for review before their in-person HBB course. All groups will receive digital versions of the HBB manual accessible through the mHBS platform.

## 5.2 PRE-COURSE ASSESSMENTS

During the pre-course period, study personnel will visit study facilities on a weekly basis (or more frequently) to observe delivery practices, number of deliveries, and will conduct a needs assessment on the preparedness of study facility and personnel to provide neonatal resuscitation.

- All study facilities will be provided with resuscitation kits as needed, based on the initial HBB equipment and resource mapping, which will be conducted during the clinical observations baseline period, before in-person HBB training courses.

The research assistant will also perform baseline knowledge tests, bag-mask ventilation (BMV) skills and standardized simulation performance assessments in all participants using the NeoNatalie Advanced Simulator (Figure 3).

**Figure 3. Neonatalie Advanced Manikin (Laerdal)**

[figure not shown]

Participant performance during the simulation will be tracked using the Simulation (BMV and OSCE) Checklists by the research assistant and by the NeoNatalie Advanced simulator with standardized performance-based feedback provided to each participant. The manikin stores training data in a database that can be accessed remotely. When feasible, research assistants doing the performance and clinical observations will be blinded to the allocation of the HCPs whom they are assessing.

## 5.3 HELPING BABIES BREATHE 2ND EDITION COURSE

All study participants will complete a traditional in-person HBB Second Edition provider training course using a NeoNatalie low-fidelity manikin training kit and provider training materials. All participants will receive course attendance fees and a HBB 2nd edition course completion certificate.

*HBB corner:* All facilities will be encouraged to set up a HBB corner for manikin-based low-dose, high-frequency practice per current HBB program recommendations. All participants in all groups will be encouraged to perform low dose, high frequency (LDHF) manikin-based practice at facility-based HBB corners per current HBB recommendations. The frequency with which

participants interact with the manikins will be tracked using self-report on the mHBS app and paper logs at the HBB corners, and with trackers if feasible.

Figure 1. Study Diagram

[figure not shown]

## 5.4 IMMEDIATE POST-COURSE ASSESSMENTS

Immediately after the HBB course, the research assistant will perform baseline knowledge tests, bag-mask ventilation (BMV) skills and standardized simulation performance assessments) in all participants using the NeoNatalie Advanced Simulator to conduct standardized simulation performance assessments.

Participant performance during the simulation will be tracked using the BMV and OSCE Checklists by the research assistant and by the NeoNatalie Advanced simulator with standardized performance-based feedback provided to each participant. The manikin stores training data in a database that can be accessed remotely. Where feasible, research assistants doing the performance and clinical observations will be blinded to the allocation of the HCPs whom they are assessing.

## 5.5 FOLLOW UP ASSESSMENTS

Participants will have ongoing access to the mHBS platform and will be sent reminders at 1, 3, and 6 months after initial NR training to take a follow-up NR knowledge test and to again participate in standardized performance simulations of bag-mask ventilation (BMV) skills and standardized simulation performance assessments conducted by research assistants who will visit their hospital facility with the NeoNatalie Advanced Simulator.

To understand the impact of educational strategies on clinical practice, clinical observations of routine care provided by participating healthcare providers will be conducted by research assistants in participating facilities using a standardized Delivery Checklist. This includes data on newborn care at the time of delivery and resuscitation (if applicable). See attached checklist. We will also gather data regarding capacity for provision of NR within facilities (e.g., number of deliveries, availability of trained staff and NR equipment), presence/absence of HBB practice corners, and rates of NR training among HCPs). We will review delivery outcomes if available from existing databases such as the Neonatal Registry before and after the HBB training. The Neonatal Registry data will be deidentified by a staff member who is not a member of the study team before release. When possible, resuscitation debriefs will be encouraged using the resuscitation debrief form and the perinatal death audit form will be used to identify the cause of death when not specified (see attached). No identifiable patient data will be stored and study facilities and participants will be identified by only by study code number.

At the end of the 6-month follow up period, participants will be asked to complete a feedback survey, designed to capture metrics related to the accessibility and utility of VR for neonatal resuscitation initial and refresher training.

## 6. STUDY INCENTIVES

All active study participants will be provided with travel (if applicable), course attendance fees and air-time to facilitate upload of study data to a secure study database during the study follow-up period. Automated reminders will be sent one week before, on the due date, and one week

after the activity is due. After the third automated reminder, two attempts will be made by the study investigators to contact the study participant using contact information provided on enrollment. If no contact is made, the study participant will be deemed inactive.

## 7. DATA MANAGEMENT

*Neonatalie Advanced Manikin* data collected during simulation sessions will be identified by study ID only. *HBB Knowledge check, BMV and OSCE Checklists* data will be entered into mHBS and RedCap. Data from paper records will be entered into RedCap after each session. Electronic copies of study data will be stored on a local password protected study computer and in a secure study database. The hard copy of all documents should be filed in a locked cabinet in the study office.

## 8. DATA ANALYSIS

Demographic data will be compared between VR, NR video, and control groups and assessed for group to group differences. Pass/Fail rates on the study evaluations: Knowledge test, bag-and-mask ventilation skills assessment (BMV), and standardized simulations of routine care and initial resuscitation (OSCE A) and prolonged resuscitation (OSCE B) done at the following time periods: Baseline, Pre-course, Immediate post-course, and at 1 month, 3 months, and 6 months in the follow up period will be calculated and compared between groups. The primary endpoint is the 6-month post-baseline evaluation. We will perform an analysis of covariance with each six-month score regressed on the baseline score of each subject and compared among the three groups.

Two post-hoc statistical tests will be performed to ascertain possible statistically significant differences between VR and Video groups with the Control group at each time point. A secondary analysis will take full advantage of the longitudinal nature of the data (see Figure 9). Here, we posit a structural response model where skills will be initially acquired uniformly by all subjects (at the immediate post-course assessment after face-to-face training) but retention of these skills will dissipate rapidly over time in the Control group, but less precipitously in the other two groups, with the least deterioration of knowledge and skills in the VR group. The statistical modeling approach in this case will be through a change-point model with random intercept and slope. The main statistical test will be the assessment of the statistical significance of the interaction between group and time, during the second period (i.e., after the change or inflection point in the curve).

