### 8.1 SAMPLE SIZE CALCULATIONS

We hypothesize that there will be a minimum 20% difference in the proportion of subjects who pass OSCE A and OSCE B, via a one-sided test at the 6-month evaluation. The desired power is 80% taking into account that two comparisons (VR vs. Controls and Video vs. Controls) will be carried out with the hypothesis that the proportions of subjects in the VR group will demonstrate performance metrics that are higher (by at least 20%) than the control group.

The alpha level has been halved so as not to inflate the type-1 error rate (of 5% overall) so 83 participants per group or a total of 249 participants will be sufficient to detect this difference under all the scenarios considered here. However, to account for study dropout, we will recruit up to 280 participants across the two country sites. We expect that the power generated by the ANCOVA procedure will be even higher as well as the power generated by the longitudinal (secondary) change-point analyses will be much more sensitive (powerful) to detect differences in each pairwise comparison. Thus the proposed sample size will likely be able to detect difference in skill retention with very high power.

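### As written, the primary 6-month ANCOVA takes nothing from participants without a 6-month score, even when their post-course, 1- and 3-month scores are held; this can bias the contrast if dropout relates to those scores differently by arm

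*Protocol*

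**What the plan says.** Protocol section 8 names the endpoint: "The primary endpoint is the 6-month post-baseline evaluation". It then names the model, in which the three groups are compared: "We will perform an analysis of covariance with each six-month score regressed on the baseline score of each subject". No visit between baseline and 6 months appears in that model.

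The same section lists the assessment times: "Baseline, Pre-course, Immediate post-course, and at 1 month, 3 months, and 6 months in the follow up period". The intermediate results have two stated uses. One is the comparison of the groups at each time point. The other is a change-point model with random intercept and slope, introduced with: "A secondary analysis will take full advantage of the longitudinal nature of the data". The main test of that model is the group-by-time interaction after the change point.

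Dropout is addressed in several places:
- Section 4.4 excludes people who will not be available or willing for follow-up through 6 months.
- Section 5.5 says participants "will be sent reminders at 1, 3, and 6 months after initial NR training", and research assistants bring the simulator to the participant's own facility.
- Section 6 provides travel and airtime support, three automated reminders and two personal contact attempts. It then says: "If no contact is made, the study participant will be deemed inactive".
- Section 8.1 adds recruits: "However, to account for study dropout, we will recruit up to 280 participants across the two country sites".

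The protocol gives no expected dropout rate and no rule for analysing participants who lack a 6-month score.

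**The concern.** The primary contrast is read at the last visit, where loss is greatest, from a model that uses only one earlier measurement. The visits that say most about a missing 6-month result are the 1- and 3-month assessments, and the primary model leaves them out. An analysis of those seen at 6 months is safe only if, given arm and baseline score, being seen is unrelated to the 6-month result. An analysis that also uses the intermediate scores needs a weaker condition, because dropout may then depend on those scores too.

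A difference between arms in who drops out is plausible. The arms receive different material. The follow-up survey in Appendix 5 asks about assigned eHBB or video refreshers and lists app and access problems as barriers to them. It also lists reasons for missing a simulation, such as seeing no need for it, that could be related to skill. If such a pattern occurred, the VR–Control or Video–Control estimate would be off in a direction that extra recruits cannot correct.

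**Working it through.** **1. The plan's own figures.** Section 8.1 gives 83 per group, 249 in total, a 20-point difference, 80% power and an alpha of 5% halved to 0.025, one-sided. The control pass rate is not stated. Assuming 60% against 80%, with pooled variance:

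n = [1.96·√(2·0.7·0.3) + 0.842·√(0.6·0.4 + 0.8·0.2)]² / 0.20² = (1.270 + 0.532)² / 0.04 ≈ 81.2, so 82 per group, close to 83. (20% against 40% gives the same. The mid-range rates need more, up to 97 at 40% against 60%.)

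Dropout allowance: 1 − 249/280 = 11.1%. Recruits per arm: 280/3 ≈ 93. On the 60% against 80% assumption, completers-only power is 0.808 at 11% loss and 0.766 at 20%. The extra recruits therefore do their job for power, up to about 11% loss.

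**2. Bias at 11% loss, by hand.** Assumptions, none of them from the documents: standardised scores; correlation r = 0.6 to 0.7 between the 3- and 6-month scores; correlation b = 0.3 to 0.5 between baseline and each later score; 11% lost from each arm after month 3, at random in VR but only from below-average 3-month scorers in Control.

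- Mean of the lower half of a standard normal: −√(2/π) = −0.798.
- Rise in the 3-month mean of Control completers: 0.11 × 0.798 / 0.89 = 0.0986.
- Part of this that reaches the 6-month mean after baseline adjustment: (r − b²) × 0.0986.
- Smallest: (0.6 − 0.25) × 0.0986 = 0.035 SD. Largest: (0.7 − 0.09) × 0.0986 = 0.060 SD.

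Control completers look too good, so VR − Control is understated by 0.035 to 0.060 SD. As a yardstick, 83 per group has 80% power for 2.80 × √(2/83) = 0.435 SD, so the bias is about 8–14% of that effect. A simulation of 6,000 trials per scenario under the same assumptions gave −0.035 to −0.057 SD.

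With 15% such loss in Control and 7% random loss in VR, the rise is 0.15 × 0.798 / 0.85 = 0.141 and the bias is 0.35 to 0.61 times that, 0.05 to 0.09 SD (11–20% of 0.435).

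**3. Other mechanisms.** A separate simulation used 93 per arm and 4,000 trials per setting. It assumed correlations of 0.4 from baseline and 0.5 to 0.75 between later visits, and a log-odds of dropout that changes by 1 per SD of the last observed score. The loss shown is the average over the two arms. Monte Carlo error is about 0.002 to 0.003.

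| Relation of dropout to score | 11% loss | 20% loss | 30% loss |
|---|---|---|---|
| None | 0.00 | 0.00 | 0.00 |
| Same in both arms, true effect 0 | 0.00 | 0.00 | 0.00 |
| Same in both arms, true effect 0.4 SD | −0.007 | −0.010 | −0.014 |
| Low scorers leave Control; unrelated in VR | −0.06 | −0.10 | −0.14 |
| Opposite in the two arms | −0.10 | −0.18 | −0.27 |

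Entries are the bias of the completers' ANCOVA in SD. An estimate using all visits stayed within 0.002 SD of the truth in every setting (within 0.005 SD in the simulation of step 2). That is expected, because dropout was made to depend on observed scores only.

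**4. Precision.** At 11% loss the all-visit estimate had a standard error about 1–3% smaller in the simulation of step 2. In that of step 3 it fell from 0.144 to 0.141 with random loss and was essentially unchanged with score-related loss. The case rests on bias, not efficiency.

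**The case against.** The strongest reply is that the protocol states a model and not a complete-case rule. The same ANCOVA could be run after multiple imputation from the intermediate scores without altering a word, and the analysis plan, which is not shown, may say so. This stands. A reader might infer that the protocol orders participants without a 6-month score to be discarded, or that the lack of a missing-data section is an error. The documents support neither. What can be said is that the model, as written, takes nothing from them.

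A reader might also infer that over-recruitment is the only answer to dropout. It is not: eligibility, on-site visits, reminders and personal contact are all provided. They reduce loss, but they do not adjust the contrast for whatever loss remains.

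Nor does any link between score and dropout bias the comparison materially. The relation has to differ between arms, and the documents hold no data showing that it will. The Appendix 5 barriers do not include poor skill, and not feeling a need for practice could point to good skill. The one-arm mechanism in the working is constructed. Even there, the bias at 11% loss is modest beside sampling error: the standard error is √(2(1 − b²)/83) = 0.134 to 0.148 SD, so the bias is about 0.26 to 0.41 standard errors. In that scenario it runs against VR. The reverse pattern would flatter VR, and nothing in the protocol says which is likelier.

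Finally, the secondary random-effects model does keep people without a 6-month score. That is true, but it tests a difference in slope after the change point. Neither it nor the comparisons at each time point repair the primary 6-month contrast.

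**Conclusion.** The point holds in a limited form. The stated primary model leaves out scores that the trial collects and that bear directly on missing 6-month results, and nothing else stated in the protocol corrects the primary contrast for arm-differential, score-related dropout. The likely size is small to moderate: about 0.035 to 0.06 SD at the 11% loss that recruitment allows for, 0.10 to 0.14 SD at 20–30% loss under the one-arm mechanism, and up to 0.27 SD if the relation runs in opposite directions in the two arms. It is at most about 0.014 SD if the relation is the same in both arms, and zero if dropout is unrelated to score.

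These figures rest on assumed correlations, dropout rates and mechanisms. It would go too far to conclude that the primary result will be biased, or biased in favour of VR. The recommendation rests on the weaker missingness assumption and the low cost of the change.

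**What to change.** Keep the 6-month endpoint and the two comparisons with Control, and change how they are estimated. Either of two routes will do:

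- **Repeated-measures model.** Fit a likelihood-based model to the post-course, 1-, 3- and 6-month scores, with visit as a category, group-by-visit and baseline-by-visit terms and an unstructured covariance. Read the VR–Control and Video–Control contrasts at 6 months. Enter the post-course score as an outcome, not a covariate, because the study materials are given before the course.
- **Multiple imputation.** Impute missing 6-month results from baseline and the intermediate scores, by arm, then run the stated ANCOVA. The same imputation serves the pass/fail comparison if that is the primary scale; a logistic mixed model is the alternative.

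Keep the observed-case ANCOVA as a sensitivity analysis. Report 6-month completion by arm and by last observed score, so that readers can see whether dropout differed between arms.

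Cost: analysis wording and somewhat more programming; every score is already collected. Both routes assume that missingness depends on observed scores. If it depends on the unseen 6-month performance, the bias is reduced but not necessarily removed.

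### The secondary change-point model starts from equal skill in all arms after the course, although VR and video are given before it; fitted that way, a lasting head start would appear as better retention

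*Protocol*

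**What the plan says.** Section 3 states the aim as to "assess the impact of mobile VR simulation used before and after initial NR training". Section 5.1 (text below Figure 2) gives access to materials according to "group assignment of VR (eHBB), NR video or Control groups for review before their in-person HBB course". Section 5.5 continues access to the platform after the course. The active arms can therefore differ from control both in the level reached at the course and in the decline afterwards.

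Section 8 plans three things that matter here:

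- The primary analysis, at 6 months, is an "analysis of covariance with each six-month score regressed on the baseline score of each subject", compared among the three groups.
- VR and Video are each compared with Control at every assessment, and the listed assessments include the one immediately after the course.
- The secondary analysis proceeds "through a change-point model with random intercept and slope". It posits that "skills will be initially acquired uniformly by all subjects (at the immediate post-course assessment after face-to-face training", with loss afterwards fastest in Control and slowest in VR. Its main test is "the assessment of the statistical significance of the interaction between group and time, during the second period".

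Section 8.1 adds that the change-point analysis will be much more powerful for each pairwise comparison. It gives no slopes, standard deviations or post-course differences for that analysis.

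**The concern.** The uniform-acquisition premise sets aside the pre-course half of the intervention. If VR or video used before the course raises the skill reached at the course, the arms do not start the second period level. A model that nevertheless gives them one common post-course mean has nowhere to put the difference except the later slope. Arms that decline in parallel would then be reported as differing in retention.

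Retention is one of the trial's named hypotheses (Section 1), so the error would fall on a result that readers will look for. No arm difference in level at the change point is named in this model, either as a parameter or as a test, so the written plan contains nothing that would reveal the problem.

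**Working it through.** **The plan's own figure.** The change-point analysis has none. The only figure is 83 per group for the 6-month pass proportions (Section 8.1). The control rate is not stated. With assumed rates 0.20 and 0.40, one-sided alpha 0.025 and 80% power, the pooled formula gives n = [1.96·√(2·0.3·0.7) + 0.842·√(0.16 + 0.24)]² / 0.2² = (1.270 + 0.532)² / 0.04 ≈ 81.2, so 82, close to 83. I use 83 only as the arm size.

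**Inputs from the protocol.** Visits at t = 0, 1, 3 and 6 months after the course, so Σt = 10 and Σt² = 46; random intercept and slope; 83 per arm; one-sided 0.025.

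**Assumptions (the protocol gives no values).** A continuous score with total SD 1 at the post-course visit. Set A: intercept SD 0.8, residual SD 0.6. Set B: 0.71 and 0.71 (within-person correlation 0.5). Random-slope SD s from 0 to 0.10 per month. Where baseline is in the model, it is one measurement with equal arm means. Truth: VR gains d at the course, keeps it, and declines exactly in parallel with control.

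**Step 1: common post-course level fitted.** With k visits in the model (4 without baseline, 5 with), intercept variance τ² and residual variance σ², let c = τ²/(σ² + kτ²). The expected slope difference by generalised least squares is

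d · 10(1 − 4c) / (46 − 100c),

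although the true slope difference is 0.

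- Set A, no baseline: c = 0.64/2.92 = 0.219, bias 0.051d per month.
- Set A, with baseline: c = 0.64/3.56 = 0.180, bias 0.100d.
- Set B, no baseline: c = 1/5, bias 2/26 = 0.077d.
- Set B, with baseline: c = 1/6, bias 3.33/29.33 = 0.114d.

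The random-slope SD does not change the bias. It enters the standard error, SE = √{(2/83)·[σ²/(46 − 100c) + s²]}, and the rejection rate is 1 − Φ(1.96 − bias/SE).

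| Set | Baseline in model | s | SE | d = 0.2 | d = 0.3 | d = 0.5 |
|---|---|---|---|---|---|---|
| A | yes | 0.05 | 0.0192 | 18% | 35% | 74% |
| A | yes | 0.10 | 0.0235 | 13% | 25% | 57% |
| A | no | 0.05 | 0.0205 | 7% | 11% | 24% |
| A | no | 0.10 | 0.0245 | 6% | 9% | 18% |
| B | yes | 0 | 0.0203 | 20% | 39% | 80% |
| B | yes | 0.10 | 0.0255 | 14% | 27% | 60% |
| B | no | 0 | 0.0215 | 11% | 19% | 43% |
| B | no | 0.10 | 0.0265 | 8% | 14% | 30% |

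Every entry should be 2.5%. Example (first row, d = 0.5): bias 0.0501, 0.0501/0.0192 = 2.61, 1 − Φ(1.96 − 2.61) = 74%.

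**Step 2: level free by arm.** The expected slope difference is 0 and rejection is 2.5% for every d. The SE becomes √{(2/83)·[σ²/21 + s²]}, where 21 = 46 − 10²/4. For Set A this is 0.0218 (s = 0.05) or 0.0256 (s = 0.10).

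**Step 3: price of the free level if acquisition really is uniform** (Set A, baseline in the model). For a true slope difference of 0.08 per month, power goes from 99% to 96% (s = 0.05) or from 93% to 88% (s = 0.10). For 0.05 per month it goes from 74% to 63%, or from 57% to 50%.

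**The case against.** **The wording may be an expectation, not a constraint.** The same sentence also posits how fast each arm loses skill, and that is what the model goes on to test. Whether a group effect enters at the change point is detail that an analysis plan could settle. This stands: the document does not say that the common level is fitted, so the false slope is conditional on that reading. But the premise conflicts with pre-course release on either reading, and it is the only statement the protocol makes about the arms' level at the change point.

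**The trial does not rest on this model.** A reader might infer that a lasting gain from pre-course use would be missed. It would not. The primary 6-month ANCOVA and the VR and Video comparisons with Control at each visit, including immediately after the course, would show it.

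**A slope test is a proper retention test.** A reader might count it as a failure that, with the level free, the slope test rejects in only about 2.5% of trials when the arms decline in parallel. That is the right answer to the retention question. For the same reason, replacing the slope by a 6-month contrast as the main test would largely duplicate the primary analysis and is a matter of preference.

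**The size must come from the model named.** Ordinary least squares would give 10/46 = 0.22d per month. The protocol specifies random effects, under which the bias is a quarter to a half of that.

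**Conclusion.** The point holds for the secondary change-point analysis. Its equal-start premise contradicts the pre-course release of VR and video and the stated objective. If the premise is fitted, a lasting gain d with parallel decline is turned into a false retention difference of about 0.05d to 0.11d per month. For d of 0.2 to 0.5 SD, one-sided rejection is about 6-43% without baseline in the model and 13-80% with it, against 2.5%. With the level free, the slope test is valid but covers only retention.

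These sizes rest on assumed SDs, a continuous score, complete data and a gain that persists in full. The direction does not depend on the particular SDs tried. The claim of much greater sensitivity is unsupported as written, since no slopes or SDs are given for it. It would be too strong to say that it fails unless acquisition is uniform: with a free level, the power of the slope test depends on the slope difference and the variances, not on equal starting levels. The primary conclusion of the trial is not affected.

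**What to change.** In Section 8, delete the premise of uniform acquisition and state that the change-point model includes a group effect on the post-course level. Keep the second-period group-by-time interaction, labelled as the test of retention. Report it together with the arm difference in post-course level, and give the model-based 6-month difference as supportive. In Section 8.1, remove the statement that this analysis will be much more sensitive, or support it with the slopes, SDs and correlations assumed.

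The cost is a change of wording and one extra parameter per active arm. If acquisition truly is uniform, the slope test loses some power: about 3 to 11 percentage points in the Set A examples with baseline in the model.
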